#### Assessment of mt-HBT overall HCC sensitivity

All eligible and evaluable participants with a valid mt-HBT result and a confirmed HCC reference result will be included in the secondary analysis of mt-HBT overall HCC sensitivity. The analysis will include all confirmed HCC cases from both the ultrasound and CT/MRI screening arms and will be based on Visit 1 results. mt-HBT overall HCC sensitivity will be evaluated as the proportion of mt-HBT High results among participants with confirmed HCC status. A point estimate with 2-sided Wilson score 95% CI will be calculated for the mt-HBT overall HCC sensitivity.

#### Other prespecified analyses

mt-HBT positive and negative predictive values, positive and negative likelihood ratios, and area under the receiver operating characteristic curve will be calculated using the observed mt-HBT sensitivity and specificity, as well as HCC prevalence, where applicable. The impact of HCC prevalence on predictive values will also be assessed for varying prevalence values.

Point estimates with 95% confidence intervals will be calculated for mt-HBT HCC sensitivity and specificity, with stratification by tumor stage (eg, BCLC, Milan criteria), tumor size (<2 cm vs. 2–3 cm vs. 3–5 cm), and demographic and clinical characteristics (eg, body mass index, liver disease etiology, Child–Pugh score). The same performance metrics will be calculated and compared for AFP at various cutoffs, alone or combined with ultrasound.

mt-HBT sensitivity and specificity for indeterminate or suspicious observations (ie, LR-3, LR-4) will be calculated initially based on Visit 1 observations. After completion of Visit 2 and the full follow-up period, mt-HBT sensitivity and specificity will be recalculated for the observations that resolved to confirmed HCC or non-HCC status, using a range of allowable time intervals between blood collection and the resolved clinical status reference result. Similarly, the mt-HBT early-stage HCC sensitivity, overall HCC sensitivity, and HCC specificity will be recalculated after incorporating the resolved clinical status after the follow-up period, and compared with ultrasound, AFP, or ultrasound plus AFP.

Concordance and discordance between local and central radiologists, as well as between individual central radiologists, will be assessed for all CT/MRI images undergoing central radiology review with LI-RADS classification.

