### Study definitions

For participants undergoing ultrasound screening, imaging will be assessed locally using v2017 Ultrasound LI-RADS.^25^ Ultrasound results will be classified for the study as Ultrasound Positive for US-3 LI-RADS assessments, or Ultrasound Negative for US-1 and US-2 LI-RADS assessments. The HCC status of all participants will then be determined by multiphase contrast-enhanced CT/MRI imaging with central radiology assessment using v2018 CT/MRI Diagnostic LI-RADS,^26^ or by definitive pathology when available. HCC status will be classified for the study as confirmed HCC, confirmed non-HCC, or indeterminate observation. Early-stage HCC will be defined by the Milan criteria.^27^ Although BCLC staging is widely used and will also be reported in ALTUS, it includes Eastern Cooperative Oncology Group (ECOG) performance status and Child–Pugh status, which are independent of tumor burden. Improvements in cancer screening efficacy using blood-based biomarkers can impact tumor burden at the time of diagnosis, but not liver function or patient performance status. Milan criteria will likely yield more objective data for the primary analysis, as it is determined by tumor burden alone and can be fully assessed using cross-sectional imaging. The category of confirmed HCC will be restricted to pathology-confirmed HCC or central radiology classifications of LR-5 or LR-TIV with assessment of definite or probable HCC. The algorithm determining the mt-HBT test result of “Negative” or “High” was developed in previous work and locked before the evaluation of ALTUS results.^23^ A full list of study definitions is provided in Table 1.

**TABLE 1 T1:** ALTUS study definitions

Study term	Definition
Ultrasound positive^a^	• US-3 (Positive)
Ultrasound negative^a^	• US-1 (Negative) • US-2 (Subthreshold)
mt-HBT high	• mt-HBT result indicating an elevated likelihood of HCC
mt-HBT negative	• mt-HBT result indicating a lower likelihood of HCC
Confirmed HCC^b^ ^c^	• Pathology-confirmed HCC or cHCC-CCA, regardless of LI-RADS category • LR-5 • LR-TIV with definite or probable HCC^d^
Confirmed non-HCC^b^ ^c^	• Pathology-confirmed malignancies other than HCC or cHCC-CCA • Pathology-confirmed benign observations • No observation/LR-Negative • LR-1 • LR-2
Indeterminate observation^b^	• LR-NC (not categorizable) • LR-3 • LR-4 • LR-M • LR-TIV without definite or probable HCC^4^

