#### Longitudinal follow-up

Clinical, lab, and imaging data, including standard-of-care screening imaging visits, will be collected for each participant up to 18 months from enrollment. Any CT/MRI imaging performed as part of clinical care during the longitudinal follow-up period will be collected and will undergo the same central radiology review process as in Visit 1 and Visit 2. For participants diagnosed with HCC, treatment and outcomes data will be collected during the follow-up period.

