Several countries have implemented national screening programs from which real-world evidence suggests associations with early HCC detection and improved survival.^52^^–^^57^ Indications of likely benefits from screening have been demonstrated despite low adherence and sub-optimal early-stage sensitivity of ultrasound-based screening, both of which may potentially be improved upon by blood-based screening.^22^^,^^58^ Modeling of such improvements suggests substantial comparative benefits of mt-HBT screening on early-stage HCC detection and life years gained, with the potential for cost-effectiveness.^59^^,^^60^ While further study is needed to fully understand the extent of physical, psychosocial, and economic harms, analyses to date have not found the severity of harms to outweigh the perceived benefits of HCC screening.^22^^,^^61^^–^^65^ Specific aspects of existing guideline recommendations have also been developed to minimize harms associated with cross-sectional imaging and biopsy, as well as to minimize overdiagnosis.^61^ If satisfactory sensitivity and specificity characteristics of the mt-HBT can be demonstrated in ALTUS, it would support the likelihood that blood-based screening may improve early-stage HCC detection without substantially increasing harms. In addition, it may potentially help to reduce certain harms. For example, an understanding of biomarker profiles in participants with indeterminate imaging observations may enable risk stratification to optimize biopsy recommendations or additional screening.^61^ There are also indications that liquid biopsy tests such as the mt-HBT may be less likely than cross-sectional imaging to detect indolent cancers of low clinical significance, potentially reducing the risk of overdiagnosis.^61^^,^^66^^–^^69^ ALTUS will provide informative data to help address these and other important questions about blood-based screening.

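### The follow-up analysis of resolved LR-3/LR-4 observations omits lesions that stay LR-3/LR-4 without pathology, so its analysis set is selected on outcome

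*Protocol article*

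**What the plan says.** All references are to the protocol article.

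- **Study definitions, Table 1.** The text says "A full list of study definitions is provided in Table 1". Confirmed non-HCC requires pathology showing another malignancy, or one of: "Pathology-confirmed benign observations • No observation/LR-Negative • LR-1 • LR-2". The indeterminate class includes "LR-NC (not categorizable) • LR-3 • LR-4 • LR-M". No entry depends on elapsed time or on stability.
- **Longitudinal follow-up.** Clinical, laboratory and imaging data "will be collected for each participant up to 18 months from enrollment". CT/MRI done in clinical care during that period "will undergo the same central radiology review process as in Visit 1 and Visit 2". The section on Screening Visit 2 does not require reference CT/MRI for everyone.
- **Other prespecified analyses.** LR-3/LR-4 performance is first calculated on Visit 1 observations. After follow-up, "mt-HBT sensitivity and specificity will be recalculated for the observations that resolved to confirmed HCC or non-HCC status". The time allowed from blood draw to reference label is varied in this step, which is described as "using a range of allowable time intervals between blood collection and the resolved clinical status reference result". Early-stage sensitivity, overall sensitivity and specificity are then updated in the same way with the resolved status.
- **Discussion.** The article expects that "an understanding of biomarker profiles in participants with indeterminate imaging observations may enable risk stratification to optimize biopsy recommendations".

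**The concern.** The two ways out of the indeterminate class are not symmetric. A lesion that progresses to LR-5 leaves as HCC. A lesion that does not progress leaves as non-HCC only if it also regresses to LR-1/LR-2, disappears, or has pathology. One that is simply read again as LR-3 or LR-4 is never scored. Widening the allowed interval between blood draw and reference result does not help, because no interval reclassifies an unchanged lesion.

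This is a different matter from missing follow-up imaging. A participant with complete repeat CT/MRI is still left out. At Visit 1 an LR-3/LR-4 observation has no HCC status unless pathology is available, so follow-up is the main source of a reference label for this group. Risk stratification before biopsy, the use named in the Discussion, is a predictive-value question in the population that the rule thins out.

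**Working it through.** The plan states no figure for this analysis, so there is none to reproduce.

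**Inputs.** From the article: mt-HBT sensitivity 65% (Sample size and statistical power) and specificity 87% (the case-control validation cohort in the Introduction). Assumed, because the article gives no outcome mix: of all LR-3/LR-4 observations, a share h = 15% become confirmed HCC, a share s = 20%, 45% or 60% stay unchanged without pathology, and the rest, r = 1 − h − s, become confirmed non-HCC.

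**Step 1: positive predictive value (PPV), with no HCC among stable lesions and the same specificity in every group.**

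Resolved-only PPV = 0.65h / (0.65h + 0.13r).

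PPV with stable lesions counted as non-HCC = 0.65h / (0.65h + 0.13(1 − h)) = 0.0975 / (0.0975 + 0.1105) = 46.9%.

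| s | r | Resolved-only PPV | Stable counted as non-HCC |
|---|---|---|---|
| 20% | 65% | 0.0975/0.1820 = 53.6% | 46.9% |
| 45% | 40% | 0.0975/0.1495 = 65.2% | 46.9% |
| 60% | 25% | 0.0975/0.1300 = 75.0% | 46.9% |

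A second set of assumptions (h = 20%, r = 30%, s = 50%, sensitivity 82% from the case-control cohort) gives 0.164/0.203 = 80.8% against 0.164/0.268 = 61.2%.

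**Step 2: when the excess disappears.** Let g be the share of stable lesions that are HCC. With equal test performance across groups, PPV depends only on HCC frequency. That is h/(h + r) in the resolved set and h + gs overall. The two are equal when g = h/(h + r):

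- s = 20%: 15/80 = 18.8%
- s = 45%: 15/55 = 27.3%
- s = 60%: 15/40 = 37.5%
- second set of assumptions: 20/50 = 40%

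Above these values the resolved-only PPV is too low.

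**Step 3: specificity.** If stable non-cancers test High at 13%, as the others do, specificity stays at 87% and only the HCC frequency changes. If their rate f differs, specificity over all non-progressing lesions is (0.87r + (1 − f)s)/(r + s), with r + s = 0.85:

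| s | f = 20% | f = 5% | Resolved only |
|---|---|---|---|
| 20% | (0.5655 + 0.160)/0.85 = 85.4% | (0.5655 + 0.190)/0.85 = 88.9% | 87% |
| 45% | (0.3480 + 0.360)/0.85 = 83.3% | (0.3480 + 0.4275)/0.85 = 91.2% | 87% |
| 60% | (0.2175 + 0.480)/0.85 = 82.1% | (0.2175 + 0.570)/0.85 = 92.6% | 87% |

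The bias can go either way, and the article does not say which.

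**Step 4: sensitivity.** If a share g of stable lesions is HCC and those cancers test High at rate t, sensitivity over all HCCs is (0.65h + t·gs)/(h + gs). It equals the resolved-only 65% only if t = 65% or g = 0. The extreme case counts every unresolved lesion as HCC. With 13% of them testing High, it gives (0.0975 + 0.13s)/(0.15 + s): 0.1235/0.35 = 35%, 0.1560/0.60 = 26% and 0.1755/0.75 = 23%. The bounds are therefore wide, which is what the resolved-only figure conceals.

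**The case against.** Several readings go further than the documents allow.

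- **That an unchanged LR-3/LR-4 lesion can never become confirmed non-HCC.** It can, through pathology showing a benign finding or another malignancy. The gap concerns unchanged lesions without pathology.
- **That the planned measures are inflated because the set is enriched for HCC.** The measures named for the resolved set are sensitivity and specificity, which do not depend on HCC frequency. Participants, providers and central readers are blinded to mt-HBT, so the result cannot itself drive which lesions resolve. Omission alone does not bias these measures; a different High rate in the omitted lesions is needed. The article also plans predictive values over varying prevalence.
- **That stability means absence of cancer.** Nothing in the article says so, and it calls these observations indeterminate or suspicious. Scoring un-upgraded lesions only as non-HCC would replace one debatable reference with another. It would also depend on late CT/MRI that the study does not require.
- **That the trial's main conclusions are affected.** The primary and secondary analyses use Visit 1 results, and the article calls the analyses supported by Visit 2 exploratory.

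All four replies stand and limit the point. It is also fair to say that handling of unresolved observations is often left to a statistical analysis plan, which is not shown here. That does not dispose of the matter: the article itself fixes both the status definitions and the analysis set, and the selection follows from the two together. The multiple imputation under Missing data is optional and is not directed at these lesions.

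**Conclusion.** The point holds within limits. By the stated rules, an LR-3/LR-4 observation that stays in that category without pathology is left out of the follow-up recalculations, however complete its imaging. The analysed set is therefore selected on outcome.

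The direction of any specificity bias is unknown, and sensitivity is at risk only if some omitted lesions are HCC. The PPV excess, about 7 to 28 points in Step 1, rests on an assumed outcome mix and on no stable lesion being HCC. It falls to zero at the break-even shares in Step 2. It concerns a use the Discussion invites, not a measure the plan names for this set. What the resolved-only result can support about indeterminate lesions is limited accordingly.

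**What to change.** For the follow-up analyses only:

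1. Report how many LR-3/LR-4 observations are never resolved, split into re-imaged and unchanged versus not re-imaged, with the mt-HBT results in each group.
2. Show the resolved-only sensitivity and specificity, and the updated overall figures, beside two bounding analyses: all unresolved observations counted as non-HCC, and all counted as HCC.
3. State that predictive values for indeterminate lesions will not be derived from the resolved-only set alone.

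The cost is a few sentences of analysis text and extra runs on central reads and test results already collected. The downside is wider and less favourable bounds. The Visit 1 primary and secondary analyses stay as they are.

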#### Missing data

All eligible and evaluable participants will be included in each analysis. Any patterns of missing data will be evaluated, and sensitivity analyses may be performed utilizing multiple imputation to assess the potential impact of missing data.

## DISCUSSION

This multicenter prospective validation study will provide novel data to inform the inclusion and positioning of the mt-HBT as a blood-based option among patients who meet established criteria for HCC screening. A major strength of the study is that all participants undergo standard-of-care screening imaging, blood collection for the mt-HBT, and contrast-enhanced multiphase cross-sectional reference imaging. In addition, the study employs a robust system for central radiology assessment in which every cross-sectional image is read by 2 independent fellowship-trained radiologists who are blinded to each other and to the local radiology reads. In case of discordance, differences are adjudicated by a third expert radiologist. Other strengths include the number and anticipated diversity of study sites and participants, robust sample size, and the direct comparative performance assessment of the mt-HBT against ultrasound for early-stage HCC sensitivity.

Within the context of the Early Detection Research Network (EDRN) 5-phase framework for biomarker development, phase 5 randomized controlled trials (RCTs) are generally considered the gold standard for establishing a reduction in cancer mortality to support widespread test adoption.^43^^,^^44^ A rationale for a phase 5 RCT is that demonstrating earlier detection alone may, in some cases, be insufficient to infer mortality reduction and other benefits. A recent study across cancer types reported that the correlation between late-stage cancer incidence and cancer-related mortality varies substantially by cancer type.^45^ Factors such as ineffective treatments, poor adherence, economic costs, morbidity associated with the test or diagnostic follow-up procedures, and overdiagnosis may contribute to a lack of overall benefit despite an observed cancer stage shift.^43^ However, HCC and the existing screening paradigm have specific characteristics that make a phase 5 RCT comparing screening with the absence of screening impractical. Notably, a significant HCC mortality benefit from screening of patients with chronic HBV infection has been demonstrated in an RCT.^46^ While no comparable trial exists for patients with cirrhosis, such a trial was attempted and found to be infeasible due to patient preferences for screening and the routine incorporation of screening recommendations into clinical care by providers, consistent with clinical practice guidelines.^47^ Contemporary trials are therefore more likely to evaluate the comparative performance of different screening modalities, and other trials such as those comparing ultrasound to abbreviated MRI or blood-based biomarker panels are ongoing.^48^^–^^51^

Several countries have implemented national screening programs from which real-world evidence suggests associations with early HCC detection and improved survival.^52^^–^^57^ Indications of likely benefits from screening have been demonstrated despite low adherence and sub-optimal early-stage sensitivity of ultrasound-based screening, both of which may potentially be improved upon by blood-based screening.^22^^,^^58^ Modeling of such improvements suggests substantial comparative benefits of mt-HBT screening on early-stage HCC detection and life years gained, with the potential for cost-effectiveness.^59^^,^^60^ While further study is needed to fully understand the extent of physical, psychosocial, and economic harms, analyses to date have not found the severity of harms to outweigh the perceived benefits of HCC screening.^22^^,^^61^^–^^65^ Specific aspects of existing guideline recommendations have also been developed to minimize harms associated with cross-sectional imaging and biopsy, as well as to minimize overdiagnosis.^61^ If satisfactory sensitivity and specificity characteristics of the mt-HBT can be demonstrated in ALTUS, it would support the likelihood that blood-based screening may improve early-stage HCC detection without substantially increasing harms. In addition, it may potentially help to reduce certain harms. For example, an understanding of biomarker profiles in participants with indeterminate imaging observations may enable risk stratification to optimize biopsy recommendations or additional screening.^61^ There are also indications that liquid biopsy tests such as the mt-HBT may be less likely than cross-sectional imaging to detect indolent cancers of low clinical significance, potentially reducing the risk of overdiagnosis.^61^^,^^66^^–^^69^ ALTUS will provide informative data to help address these and other important questions about blood-based screening.

The ALTUS study design will provide high-quality evidence on the performance and potential value of the mt-HBT. Of note, similar prospective cross-sectional screening studies have been successfully conducted for regulatory and reimbursement assessment of novel biomarker tests designed to detect other cancers.^70^^–^^73^ All participants in such studies generally undergo prospective sample collection along with diagnostic procedures to establish reference results for the test’s operating characteristics (ie, sensitivity and specificity). ALTUS represents a version of this study design and has both advantages and limitations relative to other approaches, such as retrospective repository studies or prospective clinical utility studies that limit diagnostic procedures to patients with positive test results. A major strength of ALTUS is the ability to efficiently and rigorously assess sensitivity and specificity in a large, prospective sample from the intended use population. In addition, tumor characteristics near the time of sample collection can be evaluated for both test-positive and test-negative cases, enabling subgroup performance analyses by tumor size and other metrics. In contrast, retrospective repository studies must accumulate samples and wait for clinical diagnoses to establish cases and controls for analysis, and tumor characteristics may not be known at the time a biomarker test becomes positive. Similarly, performance estimates in repository studies and clinical utility studies may be less accurate without all participants receiving diagnostic procedures to establish true negative and false negative test results. However, it is acknowledged that ALTUS does not assess how mt-HBT results may impact real-world longitudinal clinical management of patients, as results are not returned to providers in the study. In addition, it is possible that the application of diagnostic cross-sectional imaging to all participants may result in the detection of a disproportionate number of very-early HCCs (<2 cm), which are less likely to be detected by ultrasound or blood-based tests. In this scenario, the clinical significance of the apparent ultrasound and mt-HBT HCC sensitivity may be more challenging to interpret relative to sensitivity for larger HCCs that are still early-stage but at greater risk of consequential progression before the next screening interval. This emphasizes the importance of understanding performance by tumor size and highlights the potentially large impact of differences in screening adherence.

There is an urgent need to address the substantial public health burden imposed by HCC. Imaging-based screening modalities can be onerous and associated with low patient adherence, whereas a blood-based test may facilitate the incorporation of HCC screening in the current workflow of patients with cirrhosis, who routinely undergo blood tests to assess liver function. The available evidence for the utility of HCC screening, together with the potential for improvement over imaging-based screening paradigms, underscores the relevance and importance of the ALTUS study. Demonstration of favorable mt-HBT performance relative to ultrasound using a robust prospective study design may advance support for blood-based screening as a viable approach to improve outcomes for patients at elevated risk for HCC.
